### Genotyping and bioinformatic analysis

Peripheral whole blood will be collected and labeled with a unique barcode to ensure anonymization and unbiased assessment. High quality genomic DNA will be extracted using commercial kits (Qiagen) and will be quantified by spectrophotometry using Nanodrop 1000 (Thermo Fisher). Ultrasensitive targeted NGS of extracted DNA (40 ng) will be performed using custom QIAseq Targeted DNA Panel (Qiagen) containing primers for the enrichment of the 228 SNPs of interest. The produced molecularly barcoded libraries will be quantified by Qubit 3 Fluorometer (Invitrogen) and real time PCR (QIAseq Library Quant Assay kit). Sequencing will be performed by sequencing by synthesis (SBS) chemistry on MiniSeq Platform of Illumina using the MiniSeq Mid Output Kit (300-cycles). The generated NGS data (in fastq format) will be analyzed with the CLC Genomics Workbench (Qiagen) bioinformatics software and the genotype of each SNP will be determined.

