### Statistical considerations

#### Sample size estimation and endpoints of the study

The primary endpoint of the study is to discover potential correlations of the SYNTAX score with patients' genomic profile and create a blood-based gene expression test (genetic SYNTAX score) which could accurately identify patients at high risk for CAD of moderate or high severity. For the estimation of the sample size the G*Power [25, 26] and Epi Info (StatCalc) [27] software tools were used. To this regard, we made use of the exact sampling distribution of the squared multiple correlation coefficient implemented in G*Power assuming 250 predictors, a two-tailed test, power of 0.9, significance level of 0.05, ρ^2^ = 0.13 and a ratio of unexposed to exposed equal to 2 (based on a pilot study on 100 patients). The initial sample size was finally increased by 10% because of the possibility that some patients might be lost to follow-up. Hence, we aim for a total sample of 1080 patients.

Secondary endpoints of the study are the development of a panel of genetic markers that, in conjunction with clinical parameters, could strongly predict the occurrence of MACCE or any bleeding events during follow up.

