The model building process will be based on *Hurdle Models* that are a class of modeling techniques able to handle excess zeros and overdispersion of SYNTAX score variable. Describing briefly, the *Hurdle Model* has two parts: (*i*) a *zero hurdle part* which models the right-censored outcome SYNTAX score variable indicating patients with a zero-count ($$Y = 0$$) or patients with a positive count ($$Y = 1$$), where all values larger than zero are censored (i.e. fixed at one) and (*ii*) a *truncated count part* modeling the total number of SYNTAX score for patients presenting a non-zero count ($$Y > 0$$). Regarding the identification of the best set of predictors for each part of the model, a feature selection search strategy based on *Akaike Information Criterion* will be utilized, in which the set of predictors are included in the *full model* and at each step of the iterative process, a predictor is dropped out. To assess the fitting performance of the final model, well-known evaluation metrics for regression (e.g. mean and median squared, absolute and percentage errors) and classification tasks (*accuracy*, *F*-*measure*, *G*-*mean*, *precision* and *recall*) will be used, whereas for the evaluation of the prediction performance of the model, data-generating schemas (i.e. *holdout* and *k-fold cross-validation*) that split the available dataset into training and test sets will be performed. In addition, graphical evaluation of model’s performance will be assessed through appropriate visualization methods, such as *Receiver Operating Characteristic* (ROC) and *Precision-Recall* curves for the zero-hurdle part and *Regression Error Characteristic* (REC) curves for the truncated count part.

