*Survival analysis* methods will be also performed for examining patients at follow-up period. More specifically, the non-parametric *Kaplan–Meier* analysis will be conducted for graphically evaluating the survival function of patients, while *log-rank tests* will be conducted for investigating effects of different factors on survival distribution. Finally, *Cox Regression* analysis will be performed to build a multivariate regression model between several predictors and the survival time of patients.. Statistical analysis will be performed via the R statistical programming language. In all tests a difference will be considered as statistically significant when p-value (significance) will be less than 0.05, while all conducted tests will be two-tailed (non-directional).

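### The genetic panel for MACCE or bleeding has no stated selection rule, multiplicity control or out-of-sample check; if its predictors are drawn from the 228 SNPs on the same data, its apparent prediction will be optimistic

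*Protocol article*

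**What the plan says.** Under *Sample size estimation and endpoints of the study*, the protocol article makes the secondary endpoint the development of a genetic marker panel that, together with clinical parameters, "could strongly predict the occurrence of MACCE or any bleeding events during follow up". The genotyping section describes a custom sequencing panel "containing primers for the enrichment of the 228 SNPs of interest".

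The last paragraph of *Statistical analysis* is the only analysis text for follow-up outcomes. It names Kaplan–Meier curves, log-rank tests "for investigating effects of different factors on survival distribution", and Cox regression to "build a multivariate regression model between several predictors and the survival time of patients". It then sets one threshold for everything: "In all tests a difference will be considered as statistically significant when p-value (significance) will be less than 0.05".

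Safeguards are described elsewhere, each for a different analysis:

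- **Bonferroni:** pair-wise Mann–Whitney comparisons of SYNTAX score.
- **Benjamini–Hochberg:** the disease-ontology enrichment analysis.
- **AIC elimination, error and classification metrics, holdout and k-fold cross-validation:** the hurdle model, a class chosen as "able to handle excess zeros and overdispersion of SYNTAX score variable". The validation schemes are those that "split the available dataset into training and test sets will be performed", and the accompanying ROC, Precision-Recall and REC curves are assigned to the two parts of that model.

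**The concern.** The secondary aim is a prediction claim, and a strong one. Evidence for such a claim has to come from data that were not used to choose or fit the predictors. The article accepts this for the SYNTAX model but says nothing comparable for the MACCE and bleeding model, where the number of candidates is large relative to the likely number of events.

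If markers are chosen from 228 candidates and the resulting Cox model is judged in the same patients at an unadjusted 0.05, a panel with no predictive value can look successful. The Abstract and Conclusion present the score as a possible guide to therapeutic strategy. The Discussion also notes that data on genetic scores for MACCE are limited, and cites a polygenic score that did not significantly improve risk classification in acute coronary syndrome. A weak or absent SNP signal is therefore a realistic outcome that the analysis should be able to reveal.

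**Working it through.** **Stated figures.** No sample size, event rate or target accuracy is given for the MACCE/bleeding endpoint, so there is no figure for it to reproduce. The total of 1080 is sized on the SYNTAX endpoint. The stated inputs (250 predictors, ρ² = 0.13, power 0.9, two-tailed 0.05) give 716 in the exact multiple-correlation test, and 716 × 1.1 = 788 or 716/0.9 = 796 after inflation, not 1080. The second sample-size tool's inputs are only partly reported, so it may have driven the total. That is a separate matter, and 1080 is taken as given here.

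**Inputs from the article.** 228 candidate SNPs; 1080 patients; follow-up at 1 year; threshold 0.05, two-tailed.

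**Assumptions.** One-year event rate 5–20%; SNPs independent; allele frequencies uniform on 0.05–0.50; every SNP null for the outcome; no loss to follow-up. The survival paragraph names neither MACCE nor bleeding, so survival time is read as time to the follow-up event.

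**Step 1: false positives.**

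- Expected null SNPs passing 0.05: 228 × 0.05 = 11.4 per endpoint, or 2 × 11.4 = 22.8 over MACCE and bleeding.
- Probability of at least one: 1 − 0.95^228 = 0.99999. Probability of at least five: 0.99.
- A Bonferroni threshold over the SNPs would be 0.05/228 = 0.00022.

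**Step 2: events per candidate SNP.**

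- At 5%: 1080 × 0.05 = 54 events; 54/228 = 0.24.
- At 20%: 1080 × 0.20 = 216 events; 216/228 = 0.95.

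**Step 3: all-null simulation.** For each of 100 replicates per event rate, 1080 patients with exponential event times censored at 1 year were generated. SNPs were screened by a Cox score test (a log-rank-type trend test) at p<0.05, and those selected were fitted in an ordinary Cox model. The C-index was computed in the same data and in 2000 new patients.

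| Event rate | Mean events | Mean SNPs selected | Apparent C-index (5th–95th percentile) | C-index, new patients |
|---|---|---|---|---|
| 5% | 52.9 | 12.0 | 0.79 (0.72–0.86) | 0.50 |
| 10% | 106.3 | 11.2 | 0.71 (0.66–0.75) | 0.50 |
| 15% | 161.6 | 11.2 | 0.67 (0.63–0.70) | 0.50 |
| 20% | 217.3 | 11.2 | 0.64 (0.61–0.69) | 0.50 |

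The Cox model's overall likelihood-ratio test was significant at 0.05 in every replicate.

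A separate simulation with 982 patients (1080/1.1) and 60 replicates per rate gave apparent values of 0.78, 0.72 and 0.65 at 5, 10 and 20%, again with 0.50 in new data.

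**The case against.** The strongest objection is that the article does not specify the procedure simulated. A reader might infer that SNPs are to be screened by log-rank tests at p<0.05 and the survivors entered in an unpenalised Cox model. The text supports neither step. It speaks of different factors and several predictors, gives no entry rule, and neither names nor rules out a penalty. The p<0.05 sentence is a general significance convention, not a selection criterion. This objection stands, and the point is worded conditionally because of it.

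A second reading also fits. The genetic score built for SYNTAX, with its cross-validation, might be carried into a Cox model with a few clinical variables. Selection would then be against SYNTAX rather than MACCE, and the optimism would be much weaker. The endpoint's wording, a marker panel developed to predict MACCE or bleeding, points more naturally to a panel built for those outcomes, but the text does not settle it.

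Third, an article condenses the full plan, and a separate analysis plan may add validation. That limits the point but does not remove it. The article does describe selection and validation, ties them to the SYNTAX model, and states one unadjusted threshold for all tests alongside an aim of strong prediction.

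Fourth, the size depends on assumptions. No event rate is given, and MACCE here includes revascularisation and all-cause death in a population that includes acute coronary syndrome, so even 20% is not a documented ceiling. The SNPs were chosen as relevant to CAD, so all-null is a worst case.

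Borrowing the AIC elimination would not rescue the Cox model. Its one-parameter threshold is about p<0.157, or nominally 228 × 0.157 ≈ 36 null SNPs, and the full starting model would have fewer than one event per SNP over the assumed rates.

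**Conclusion.** The point holds in conditional form. The article promises a panel that strongly predicts MACCE or bleeding. For it, the article states only log-rank tests, a Cox model with unstated predictor selection and an unadjusted 0.05, while the multiplicity control and validation it describes are tied to other analyses.

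If the Cox predictors are drawn from the 228 SNPs on the same data, about 11.4 null SNPs per endpoint would pass 0.05. In the worst case, the apparent C-index would average 0.64–0.79 over assumed event rates of 20% down to 5%, against 0.50 in new patients. The optimism shrinks as events increase but persists across that range. Linkage disequilibrium would change the exact counts, not the direction.

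A reader might go further and conclude that the study will report discrimination that is mostly selection noise. The documents do not support that: they commit to no discrimination measure for the Cox model, fix no selection rule, and use SNPs selected for CAD relevance, some of which may carry signal.

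**What to change.** Amend the survival paragraph of *Statistical analysis*, before follow-up outcomes are analysed, to state that:

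1. The cross-validation already described for the SYNTAX model also applies to the Cox models for time to first MACCE and, separately, for bleeding, with all SNP selection and tuning inside the resampling loop.
2. Each model is either a penalised Cox regression (ridge or elastic net) or a Cox regression with one pre-weighted SNP score and a few fixed clinical variables.
3. The report gives the cross-validated C-index, the calibration slope and the gain over a clinical-only Cox model.
4. Single-SNP log-rank results are exploratory.

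If a separate analysis plan already contains this, a sentence aligning the two is enough.

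The cost is analysis wording and some computing time, with no new patients or assays. The downsides are that reported discrimination will be lower, and a penalised model gives no conventional p-value for each SNP.

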The SYNTAX score is the best-known scoring algorithm to evaluate CAD complexity as a comprehensive angiographic grading tool taking into consideration anatomic risk factors [16]. According to the extent of CAD, this score facilitates the objective guidance of decision-making between coronary artery bypass grafting (CABG) surgery and percutaneous coronary intervention (PCI). Despite, the SYNTAX score relies on invasive coronary angiography findings and the discovery of risk stratification algorithms that facilitate non-invasive estimation of CAD complexity could alter the prognostic plan in patients with CAD.

The rationale behind this prospective study is to associate, for the first time, the severity of CAD, as assessed by the SYNTAX score, with patients’ genomic profile in a real-world setting of patients undergoing coronary angiography [16]. The desirable goal is to corroborate genomic and pharmacogenetic research on CAD exploring the potential clinical association of 228 selected SNPs with CAD and individualized response to clopidogrel and statin therapy, which could disentangle gene expression alterations in blood of patients with CAD. Ultimately, the GESS trial aspires to develop a genetic SYNTAX score that could non-invasively enable the identification of patients with complex and severe CAD after a blood-based gene expression analysis. This study is designed to contribute to recent calls for implementing genotype-guided precision medicine decisions, by aiding the clinicians to achieve improved prediction and therapy outcomes for CAD patients [3].

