### Biostatistics and disease ontology enrichment analysis

We sought to identify genes whose coding sequence and/or expression levels are affected by the selected 228 SNPs studied here. To this end, data mining was performed from dbSNP database using reutils [19, 20]. In addition, further information on genes, associated with the selected SNPs through GWAS, were retrieved from HumanMine database [21] using InterMineR [22]. Our approach led to the formation of a list with 127 genes that have been associated with the selected SNPs. Next, enrichment analysis was performed to identify statistically significant disease terms, whose involved genes are overrepresented in our gene list. Enrichment analysis, with Benjamini–Hochberg adjusted *p-value* < 0.001, was performed using clusterProfiler [23] and DOSE [24] (Figs. 1 and 2).

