### Statistical analysis

Descriptive analysis will be used to summarize the data. Specifically, results will contain statistics as mean, standard deviation, median, minimum and maximum values, whereas for categorical variables the frequency distribution tables with number of cases and percentage distribution will be presented. Statistical hypothesis testing procedures (*Kolmogorov–Smirnov* and *Shapiro–Wilk*) will be conducted for continuous variables to check, whether they satisfy the normality assumption. Given the fact that the response variable (SYNTAX score) presents a heavily-skewed and non-normal distribution with an excess number of zeros, non-parametric statistical hypothesis tests will be used for the investigation of the main effects of categorical variables on the population median values of the response variable. More specifically, the *Mann–Whitney* and *Kruskal–Wallis* followed by pair-wise comparisons through Mann–Whitney test using *Bonferroni’s correction* will be conducted. The investigation of the relationship between SYNTAX score and the set of continuous variables will be performed using the non-parametric *Spearman’s correlation coefficient*.

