Nevertheless, GWAS have only provided population-attributable risk data and could not be transferred to an individual with CAD. During the last decade, the advent of NGS has enabled researchers to perform parallel analyses of hundreds of genes in an unbiased approach [8]. This is attracting widespread attention enhancing CAD translational study and aiding to close the gap between genotype and phenotype. In 2013 the CARDIoGRAMplusC4D Consortium reported that targeted sequencing with NGS can discover rare variants with high sensitivity, rendering NGS an essential genetics approach in the post-GWA study era [38].

Apart from genetic mapping, GWAS and NGS studies have also explored the clinical utility of genetic biomarkers for the creation of genetic risk scores [10, 11, 36, 41]. These algorithms would ideally predict the severity of CAD and the subsequent adverse outcomes aiming to identify patients with potential benefit from preventive care. For their development, researchers have examined the prognostic value of blood-based genetic panels, in comparison with imaging (myocardial perfusion imaging or coronary computed tomography angiography), angiographic (visual or quantitative assessment of coronary artery stenosis or Gensini) or clinical (GRACE) predictive scores [12, 15, 42–44]. COMPASS and PREDICT trials created 2 gene-expression scores outperforming clinical factors and non-invasive imaging in discriminating patients with > 50% stenosis [45, 46]. Despite, Labos et al. reported that the addition of their developed polygenic risk score to the GRACE risk score could not significantly improve risk classification in acute coronary syndrome admissions [42]. Moreover, weighted multi-locus risk scores have been created to predict recurrent vascular events or statin efficacy and atherosclerotic burden alterations in CAD populations [10, 47–49]. Nevertheless, limited data exist about the utility of genetic risk scores for the prediction of MACCE [11–13, 41].

To the best of our knowledge, GESS is the first study yet to investigate the association of such a large number of candidate SNPs (228) with SYNTAX-score-based CAD complexity. To this end, GESS emerges as a part of a research project aspiring to complement traditional risk factor assessment with panels of significant metabolomic and genomic biomarkers [50, 51]. The co-evaluation of novel risk factors and the complexity of CAD could significantly expand the concept of cardiovascular precision medicine.

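### Significance is fixed at p < 0.05 for all tests, and no stated correction spans the 228 SNPs: up to about 11 false SNP–SYNTAX associations are expected if none is real

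*Protocol article*

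**What the plan says.** All references are to the protocol article.

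- **Threshold.** The last part of Statistical analysis states: "In all tests a difference will be considered as statistically significant when p-value (significance) will be less than 0.05". All tests are two-sided.
- **Aim.** Under Sample size estimation and endpoints, the primary endpoint is in part to "discover potential correlations of the SYNTAX score with patients' genomic profile" and in part to build a genetic SYNTAX score. The Background describes "exploring the potential clinical association of 228 selected SNPs with CAD".
- **Univariable tests.** Statistical analysis uses Mann–Whitney and Kruskal–Wallis tests for categorical variables against SYNTAX. The sentence does not name SNPs or genotypes.
- **Correction 1.** The Kruskal–Wallis test is "followed by pair-wise comparisons through Mann–Whitney test using" Bonferroni's correction.
- **Correction 2.** In the section on biostatistics and disease ontology: "Enrichment analysis, with Benjamini–Hochberg adjusted" p below 0.001. This step tests which disease terms are over-represented in the list of 127 genes.
- **Score building.** Predictors for each part of the hurdle model are selected by backward elimination on AIC. Prediction is assessed by holdout and k-fold cross-validation.
- **Secondary endpoints.** A marker panel, used with clinical parameters, that "could strongly predict the occurrence of MACCE or any bleeding events during follow up".

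**The concern.** A threshold of 0.05 for each test limits the error of that one test. Applied to 228 SNPs, it does not limit the number of false associations in the resulting list. Discovering such associations is a named part of the primary endpoint, so the list would be read as a primary result, and the article hopes it will inform precision medicine. A reader of the results could not tell which SNPs on the list reflect SYNTAX severity and which reflect chance. The article already controls the false discovery rate in a supporting bioinformatic step, yet states no such control for the clinical association tests.

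**Working it through.** The plan gives no error rate for the family of SNP tests, so it has no figure of its own to reproduce here. The sample size rests on a single joint multiple-correlation test with 250 predictors and does not bear on this point.

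**Step 1: which correction covers what.**

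| Stated correction | Family it covers | Covers the 228 SNPs? |
|---|---|---|
| Bonferroni after Kruskal–Wallis | pairs of levels within one variable | no |
| Benjamini–Hochberg | disease terms in the enrichment analysis | no |

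Take a SNP with three genotype groups (an assumption; the article does not give the coding). Bonferroni would bring its three pairwise contrasts to 0.05/3 = 0.017 each. The overall Kruskal–Wallis test for that SNP stays at 0.05, and nothing changes with the number of SNPs tested.

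**Step 2: expected false positives.** Inputs: m = 228 SNPs (Background, Genotyping, Discussion), α = 0.05 (Statistical analysis), one overall test per SNP against SYNTAX (inferred). With m0 SNPs truly unrelated to SYNTAX, the expected number of false positives is m0 × α. The article does not give m0, so a range is shown. The second column assumes independent tests.

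| m0 (assumed) | Expected false positives, m0 × 0.05 | Chance of at least one, 1 − 0.95^m0 |
|---|---|---|
| 228 (no SNP associated) | 11.4 | 0.99999 |
| 200 | 10.0 | 0.99996 |
| 150 | 7.5 | 0.9995 |
| 114 (half) | 5.7 | 0.997 |
| 50 | 2.5 | 0.92 |

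For m0 = 228, the 95% binomial range is 5 to 18 false positives. Linkage between SNPs leaves the expected number unchanged. It widens the spread and lowers the chance of at least one somewhat.

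**Step 3: with a correction across SNPs.** A Bonferroni threshold is 0.05/228 = 0.00022, which gives at most 228 × 0.00022 = 0.05 expected false positives. Benjamini–Hochberg at 5% is less strict. It limits the expected share of false positives among the declared SNPs to 5%, under independent or positively dependent tests.

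**The case against.** The strongest objections, and what stands of each:

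- **The article is silent on the SNP family, and such detail belongs in an analysis plan that is not shown.** This does not stand. A threshold for all tests is stated, not omitted, and an analysis plan that adjusted across SNPs would have to depart from it. It is true that 0.05 coexists with a Bonferroni step in the same section, so the authors do not exclude adjustment in principle. They state none for this family.
- **SNP-by-SNP testing is inferred.** This stands as a condition. The tests are described for categorical variables. Genotype is categorical and the endpoint asks for correlations with SYNTAX, so the reading is natural, but it is not written down.
- **The SNPs were preselected as relevant to CAD, and the sample size assumes a squared multiple correlation of 0.13.** This stands against any forecast of 11. A reader might infer that about 11 false SNPs will be declared, or that false discoveries are certain. Either needs nearly all SNPs to be null, which the plan does not assume. Preselection lowers the expected count without controlling it: relevance to CAD is not association with SYNTAX, and 0.13 is a joint effect that does not say how many SNPs contribute.
- **The score is built by AIC and checked by cross-validation.** This stands. A reader might infer that the 0.05 rule puts false SNPs into the genetic SYNTAX score; the documents do not support that. AIC selection does not rescue the individual claims either, since dropping a one-parameter term by AIC corresponds to a p-value of about 0.157.
- **The secondary outcomes.** A reader might count three outcomes, 3 × 228 = 684 tests and 684 × 0.05 = 34.2 false positives. The survival section speaks only of different factors and does not specify 228 tests each for MACCE and bleeding, so that total has no basis in the text.

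**Conclusion.** The point holds in a limited form. The article fixes 0.05 for all tests, and neither stated correction spans the 228 SNPs. If genotypes are tested one at a time against SYNTAX, the expected number of false associations is at most 11.4. That ceiling is reached only if no SNP is truly associated. The number falls in proportion to the count of null SNPs, which the article does not give; even with only 50 null SNPs, 2.5 false associations would be expected.

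What is affected is the set of individual SNP–SYNTAX associations that forms one part of the primary endpoint. The selection of predictors for the score and the assessment of its prediction do not use the 0.05 rule. For MACCE and bleeding, the point applies only if SNP-by-SNP tests are run.

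**What to change.** Amend the significance rule in Statistical analysis to say:

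1. A SNP–SYNTAX association is declared only at a Benjamini–Hochberg false discovery rate below 5%, computed over all 228 SNPs with one overall test per SNP.
2. Unadjusted SNP p-values may be shown but are labelled descriptive.
3. If SNPs are tested singly for MACCE or bleeding, the same rule applies within each outcome.
4. The 0.05 level stays for non-genetic comparisons, with the existing Bonferroni step for pairwise contrasts.

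No new data or patients are needed, and the model-building plan is unchanged. The cost is that fewer SNPs will be declared, including some real ones. To bound that loss, consider a SNP assumed to explain 1% of the variance, with 1,080 patients and a linear-model approximation (rough, given the skewed SYNTAX score). Power is 0.91 at p < 0.05 and 0.34 at the Bonferroni threshold of 0.00022; at 2% it is 0.997 and 0.84. The Benjamini–Hochberg cut-off is never stricter than the Bonferroni one, so the loss should be no greater than this.
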